### Study participants

2.3

IS patients admitted to Linyi Central Hospital in Shandong Province between June and December 2025 were selected as participants for this study. Eligibility was verified through a two-step process. First, trained staff screened electronic medical records of consecutive ischemic stroke patients. Second, a board-certified neurologist confirmed eligibility through a clinical assessment. Informed consent was obtained only after this verification was complete. Upon admission, patients will complete trial enrolment and sign a study informed consent form via face-to-face, followed by initiation of the 3-month intervention. Although participants are not recruited or initiating the intervention simultaneously, they will all follow the same intervention cycle.

To minimise the risk of cross-group contamination, we implemented stringent control measures across three dimensions: physical, personnel, and procedural. Physically, we allocated distinct follow-up times and consultation rooms for each group, with intervention materials kept under lock and key. Personnel-wise, all staff underwent standardised training, were explicitly prohibited from mentioning intervention details to the control group, and were provided with standardised response scripts. Procedurally, we implemented clear role-based segregation, advised patients at enrolment to avoid cross-group communication, and ensured effective execution of all isolation protocols through regular monitoring.

The study has been approved by the Ethics Committee of Linyi Central Hospital in Shandong Province (LCH-LW-2025031) and registration of the study protocol has been completed with the China Clinical Trial Registry (registration number: ChiCTR2500101457).

Inclusion criteria:

Meet the diagnostic criteria for first-episode ischaemic stroke (62);Age 18 years and above;Be able to operate smartphones and social media applications such as WeChat;Patients or family members signing an informed consent form.

Exclusion criteria:

Patients with cerebral haemorrhage after intravenous thrombolytic therapy;Patients with indications for mechanical thrombolysis by cerebral angiography (CTA) or other imaging tests (63, 64);Patients with severe mental illness, impaired consciousness, and inability to communicate effectively;Patients with severe gastrointestinal bleeding or serious cardiac, hepatic, or renal insufficiency;Patients with cancer or haemorrhagic disease.

### Sample size

2.4

The sample size was calculated *a priori* using G*Power software (version 3.1.9.7) for a two-tailed independent-samples t-test. The primary outcome was the difference in the Adherence to Refills and Medications Scale (ARMS-7) score between the intervention and control groups at the end of the study period. The following parameters were used for the calculation: Significance Level (*α*): A two-tailed α of 0.05 was considered statistically significant. Statistical Power (1-*β*): The desired power (1-β) was set at 0.80. Effect Size (Cohen’s d): Based on a review of similar literature (65, 66), we hypothesised a mean ARMS-7 score of 10.0 (SD = 2.0) in the control group and 9.0 (SD = 2.0) in the intervention group. This corresponds to a mean difference of 1.0 and a pooled standard deviation of 2.0, yielding a medium effect size (Cohen’s d) of 0.5. The sample size was calculated using the following formula:

$$n={\left(\frac{Z_{\alpha /2}+Z_{\beta }}{\Delta /\sigma }\right)}^{2}$$

Using these parameters (*α* = 0.05, power = 0.80, effect size d = 0.5), the required sample size was determined to be 32 participants per group.

To compensate for potential participant dropouts and ensure adequate power for the final analysis, we inflated the sample size by an estimated attrition rate of 20%. This resulted in a final target recruitment of 40 participants per group, for a total sample size of 80 stroke patients.

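### Section 2.4 sizes a two-group t-test with a one-sample formula: 32 per group gives about 50% power, not 80%, and the stated inputs need 64 per group

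*Protocol article*

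**What the plan says.** Section 2.4 (Sample size) of the protocol article says the calculation was done "using G*Power software (version 3.1.9.7) for a two-tailed independent-samples t-test". The quantity compared is the ARMS-7 "score between the intervention and control groups at the end of the study period".

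The inputs are stated in full:

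- Significance level: "A two-tailed α of 0.05 was considered statistically significant".
- Power: "The desired power (1-β) was set at 0.80".
- Effect: "we hypothesised a mean ARMS-7 score of 10.0 (SD = 2.0) in the control group and 9.0 (SD = 2.0) in the intervention group". The section turns this into a difference of 1.0 and d = 0.5.

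It then prints n = ((Z_alpha/2 + Z_beta) / (Delta/sigma))^2 and reports that "the required sample size was determined to be 32 participants per group". After allowing for 20% attrition it ends: "This resulted in a final target recruitment of 40 participants per group, for a total sample size of 80 stroke patients". Section 2.2 gives 1:1 allocation.

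**The concern.** The test named and the formula printed do not belong together. A difference between two independent means, with n patients in each group, has variance 2 × sigma^2 / n. The printed formula uses sigma^2 / n, which is the one-sample form. It would suit a paired design only if sigma were the SD of within-pair differences, whereas the plan uses the SD of the scores themselves. Leaving out the 2 halves the required number per group.

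What is at stake is the power claim for the primary outcome. If it is wrong by this factor, a real benefit of the size the investigators hypothesise would be missed about half the time by the named test. A reader who trusts the stated 0.80 could then take a non-significant result as evidence that the intervention does not work.

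**Working it through.** **Inputs (section 2.4; allocation from section 2.2).** Delta = 1.0; sigma = 2.0; d = 0.5; two-sided alpha = 0.05, so Z_alpha/2 = 1.960; power 0.80, so Z_beta = 0.842; 1:1 allocation; attrition 20%.

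**Step 1. Reproduce the plan's figure with its printed formula.**

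n = ((1.960 + 0.842) / 0.5)^2 = 31.4, rounded up to 32.

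32 / (1 − 0.20) = 40 per group, 80 in total.

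Both stated figures reproduce. The attrition step is done correctly; the error lies before it.

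**Step 2. Size the test that section 2.4 names.**

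- Normal approximation: n per group = 2 × 31.4 = 62.8, rounded up to 63.
- Noncentral t, the exact calculation for an independent-samples t-test: 63.8, rounded up to 64.
- With attrition: 64 / 0.80 = 80 per group, 160 in total.

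**Step 3. Power of the planned size at d = 0.5, two-sided 0.05.** The expected difference in standard-error units is d × sqrt(n/2). For n = 32 this is 0.5 × sqrt(16) = 2.0, barely above the critical value of 1.96, so power must be close to one half.

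| Evaluable per group | Power, t-test | Power, normal approximation |
|---|---|---|
| 32 | 50.4% | 51.6% |
| 40 (no dropout) | 59.8% | 60.9% |
| 64 | 80.1% | 80.7% |

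**Step 4. Difference detectable with 80% power (t-test).**

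- 32 per group: d = 0.711, and 0.711 × 2.0 = 1.42 points.
- 40 per group: d = 0.634, and 0.634 × 2.0 = 1.27 points.

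The plan assumes 1.0 point.

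**Step 5. Does any other reading give 32?** A one-sided two-group test needs 50 per group (normal approximation) or 51 (t). A two-sided one-sample or paired t-test needs 34. None of these gives 32; only the printed normal-approximation formula does.

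**The case against.** Several explanations were considered for the core figure, and none works. A 2 lost in typesetting does not explain it, because the formula as printed yields exactly 32. Nor can 32 be a total, since 40 per group and 80 overall are built on it. An unseen analysis plan does not help either, because the calculation is given in full and is wrong as given.

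The strongest remaining case concerns the analysis. Section 3 defines the primary outcome as change from baseline at 3 and 6 months, and section 5.10 lists repeated-measures ANOVA next to t-tests. An analysis that uses the baseline score could have more power than a single-time-point t-test. This is true, but the gain depends on a baseline to follow-up correlation rho that the document does not give. To reach about 80% with 32 per group the residual variance must be halved:

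- Baseline-adjusted analysis: 1 − rho^2 = 0.5, so rho is about 0.7. By normal approximation, power is 55% at rho = 0.3, 64% at 0.5, 71% at 0.6 and 80% at 0.7.
- Change score: 2(1 − rho) = 0.5, so rho = 0.75.

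These correlations are assumptions. Section 2.4 sizes the trial on an unadjusted t-test and section 5.10 names no baseline-adjusted model, so this does not justify 32. It does limit the 50% figure to the test named in section 2.4.

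Two smaller points also stand. The 50% assumes the full 20% attrition; with less, power lies between 50% and 60%. Multiple imputation does not raise that ceiling, because it does not recreate information lost with missing outcomes. And the document does not say how a non-significant result would be read, so misreading it is a risk, not a certainty.

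**Conclusion.** The concern holds. For the test, effect, SD and alpha that section 2.4 states, the required size is 64 evaluable patients per group, and the plan provides half of that. Power is about 50% at the planned evaluable size and about 60% at best, against the stated 80%. The conclusion rests only on the section's own inputs and on the t-test it names. If the primary analysis made use of the baseline score, power could be higher, by an amount the document gives no basis for fixing. In the other direction, the Discussion accepts that contamination between groups would dilute the effect, which would lower power further. The error concerns the primary outcome and must be corrected.

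**What to change.** In section 2.4, replace the formula with n per group = 2 × ((Z_alpha/2 + Z_beta) / (Delta/sigma))^2 and give the t-test result of 64 per group. Then choose one of two courses.

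1. **Enlarge the trial** to 80 recruited per group, 160 in total. This restores 80% power for a 1.0-point difference, but doubles recruitment at a single centre with a June to December 2025 admission window.
2. **Keep 80 patients and restate the design.** Say that power for a 1.0-point difference is about 50% with 32 evaluable per group (about 60% if all 40 are evaluable), and that 80% power holds only for about 1.4 points (about 1.3 with 40). Add that the result will be read from the estimated difference and its 95% confidence interval, and that a non-significant result is not evidence of no effect.

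Under either course, consider specifying a primary analysis adjusted for baseline ARMS-7 and the NIHSS randomisation stratum. This would be a new analysis choice, since section 5.10 does not contain it. It would recover part of the lost power, depending on the correlation, and should not be used to defend 32 unless that correlation is stated and supported.

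The second course costs a rewording, a less favourable stated power, and the study-leader review and ethics committee approval that section 6.8 requires for any revision. It needs no extra patients, but it corrects the claim without restoring the power.

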### Interventions

2.5

The study was divided into a control group and an intervention group, the control group received routine medical care, and the intervention group received an educational intervention based on the AI-HEALS of protective motivation theory combined with drug literacy, and the content of the intervention was designed based on the conceptual framework of the protective motivation theory combined with drug literacy, and the content of the intervention can be found in Supplementary material, and the operation diagram of the intervention system can be found in Figure 3.

**Figure 3 fig3:**
[figure not shown]
Schematic diagram of the operation of the intervention system.

The intervention comprises a three-stage core educational programme. The first session is delivered within 48 h of admission (approximately 30 min), the second is scheduled 24–48 h prior to discharge (approximately 30 min), and the third involves remote intervention via the AI-HEALS system following discharge (continuing for approximately 3 months). The intervention is delivered using a hybrid model. The initial two in-hospital sessions comprise face-to-face, one-to-one sessions between nurses and patients, utilising mobile educational services provided by the AI-HEALS system. The post-discharge session is delivered remotely via the AI-HEALS mobile application. All neurological nurses responsible for delivering the intervention underwent mandatory standardised training led by the Head Nurse and neurological physicians. This four-hour training covered the research protocol, theoretical foundations of the intervention, and operational protocols for the AI-HEALS system. To ensure intervention fidelity, the Head Nurse conducted weekly randomised spot checks of 10% of sessions via session recordings and direct observation to verify protocol adherence. To consolidate learning outcomes, the AI-HEALS system automatically delivered daily push notifications containing key medication reminders and health alerts to the intervention group for 3 months post-discharge (see Supplementary material).

## Outcomes

3

Primary Outcome: Change in medication adherence from baseline and at 3 and 6 months of follow-up.

Secondary outcomes:

Changes in medication self-behavior: medication literacy levels, correct medication taking, self-efficacy for rational medication use.Social cognitive and psychological: quality of life, depression, anxiety.Clinical health indicators: blood pressure (BP), low-density lipoprotein (LDL-C) level, glycated Hemoglobin (HbA1c), fasting plasma glucose (FPG), readmission rate.

The corresponding study questionnaires completed by all patients at baseline and follow-up were hosted on a web-based platform (Questionnaire Star). The questionnaires were distributed by the researchers through Questionnaire Star, and patients were instructed to complete them by the researchers either face-to-face (during hospitalisation) or by telephone (after discharge). Patient demographic information was collected through the case system and self-designed questionnaires.

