**Methods:**

The study will conduct a single-blind, single-centre randomised controlled trial in Linyi City Central Hospital, Shandong Province, with IS patients over 18 years old. The intervention group will receive routine care combined with the AI-HEALS, while the control group will receive routine care alone. Primary outcomes include changes in medication adherence levels at baseline and 1, 3, and 6 months of follow-up. Secondary outcomes encompass medication behavior management, medication literacy, self-efficacy, social cognition, psychological levels, and clinical outcome indicators.

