## Variables measurement

4

Socio-demographic variables will be collected from patients at baseline. Clinical reagent testing and questionnaires will be completed at baseline as well as at 3 and 6 months of follow-up, with data collection times shown in Table 2.

**Table 2 tab2:** Data collection components and collection timeline.

Data collection component		Timepoint		
		0 M	3 M	6 M
Sociodemographic variables	Age, gender, educational level, economic status, living conditions ; Duration of illness, number of medications taken, history of adverse drug reactions, source of drug information	√		
Clinical Health Indicators	BP, LDL-C, HbA1c, FPG, NIHSS	√	√	√
Medication adherence	Questionnaire: ARMS-7	√	√	√
Quality of life	Questionnaire: EuroQol-5 Dimensions 5 Levels(EQ-5D-5L)	√	√	√
Medication Literacy	ML-scale	√	√	√
Medication administration accuracy rate	Questionnaire: Medication Error Survey Form	√	√	√
Self-efficacy for Appropriate Medication	Questionnaire: Self-efficacy for Appropriate Medication Use Scale, SEAMS	√	√	√
Depression and anxiety	Questionnaire: Simplified version of the Anxiety Depression Scale (PHQ-4)	√	√	√
Readmission rate	Readmission rate			√

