### Readmission rate

5.9

Readmission rate was defined as any unscheduled admission to our hospital within 90 days of the index stroke discharge. To provide a more nuanced understanding of post-discharge outcomes, all readmissions were systematically reviewed and classified into the following predefined categories: Stroke Recurrence: Defined as a new acute neurological deficit, confirmed by neuroimaging (CT or MRI) to be a new ischemic or hemorrhagic lesion, and clinically diagnosed by a neurologist. Other Neurological Complications: Readmissions for direct sequelae of the index stroke, such as post-stroke seizures, symptomatic hydrocephalus, or progressive cerebral edema, that were not classified as a new stroke event. Cardiovascular Events: Readmissions for acute myocardial infarction, unstable angina, heart failure, or arrhythmias. Other Stroke-Related Medical Issues: Readmissions for conditions directly related to stroke management or complications, such as uncontrolled hypertension or hyperglycemia requiring hospitalization, urinary tract infection, or pneumonia. Unrelated Causes: Readmissions for reasons clearly unrelated to the stroke or its management (e.g., orthopedic injury, elective surgery). The primary outcome was the 90-day all-cause readmission rate, calculated as the total number of patients readmitted for any reason divided by the total number of discharged patients. Secondary outcomes included the readmission rates for each specific category listed above, particularly the rate of stroke recurrence.

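### The primary outcome differs between the abstract, the sample size section and the Outcomes section in visit and in form (score or change), and no test is assigned to it in the analysis section

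*Protocol article*

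**What the plan says.** The protocol article describes the primary outcome in these places:

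- **Abstract, Methods:** "Primary outcomes include changes in medication adherence levels at baseline and 1, 3, and 6 months of follow-up". No instrument is named.
- **Section 2.4, Sample size:** "The primary outcome was the difference in the Adherence to Refills and Medications Scale (ARMS-7) score". This is a score at one time point, compared by a two-sided independent-samples t-test at 0.05. The contrast is placed "between the intervention and control groups at the end of the study period", and the month is not given.
- **Section 3, Outcomes:** "Change in medication adherence from baseline and at 3 and 6 months of follow-up". This is a change, at two visits, with neither designated.
- **Section 5.9, Readmission rate:** "The primary outcome was the 90-day all-cause readmission rate". Section 3 lists readmission among the secondary outcomes.

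The schedule is otherwise consistent. Section 4 says "Clinical reagent testing and questionnaires will be completed at baseline as well as at 3 and 6 months of follow-up", and section 2.1 and Tables 1 and 2 give the same visits. None has a 1-month visit.

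Section 5.10 lists t-tests or ANOVA, rank tests, within-group paired t-tests and repeated-measures ANOVA, all at p < 0.05. It links none of them to the primary outcome or to a visit.

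Two entry conditions bear on the baseline. Section 2.3 requires patients to "Meet the diagnostic criteria for first-episode ischaemic stroke", and states "Upon admission, patients will complete trial enrolment and sign a study informed consent form via face-to-face". Section 5.1 describes ARMS-7 as four items on taking medicines and three on refilling them.

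**The concern.** A confirmatory trial needs one outcome, at one time, in one form, with one test. Here the three adherence definitions disagree on the visits (1, 3 and 6 months; end of study; 3 and 6 months) and on the form (change or score). Section 5.10 does not settle the matter. A reader of the results could not tell whether the reported primary comparison was the one fixed in advance. If a result at either visit, or in either form, could be presented as primary, the 5% error rate would not hold.

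The form matters for a second reason. Patients enrol on admission with a first stroke, so a baseline ARMS-7 score describes whatever regimen they had before the stroke. For a patient who took no medicines it may have no clear meaning, and the article gives no scoring rule for that case. A change from such a baseline compares adherence to regimens that may differ.

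**Working it through.** **1. The plan's own figure.** Section 2.4 assumes means of 10.0 and 9.0 with SD 2.0, so d = 1.0/2.0 = 0.5, with two-sided alpha 0.05 and power 0.80. The printed formula gives ((1.960 + 0.842)/0.5)² = 31.4, rounded up to 32 per group; 32/(1 − 0.20) = 40. The stated figures reproduce. They belong to the definition by score at a single time point. The printed formula lacks the factor 2 of a two-group comparison, and the named t-test needs 64 per group for 80% power. That is a separate matter; here it only explains why the reference power below is 50% and not 80%.

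**2. Definitions side by side.**

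| Place | Variable | Form | Time |
|---|---|---|---|
| Abstract | adherence | change | 1, 3 and 6 months |
| Section 2.4 | ARMS-7 | between-group difference in score | end of study period |
| Section 3 | adherence | change | 3 and 6 months |
| Section 5.9 (loose wording) | readmission | rate | 90 days |

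No two rows agree. The 1-month time in the first row cannot be collected under Tables 1 and 2.

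**3. Error rate if either scheduled visit could count.** Take two test statistics, jointly normal under the null hypothesis with correlation r, each declared significant if |Z| > 1.96. The family-wise error is 1 − P(|Z₁| ≤ 1.96 and |Z₂| ≤ 1.96). The article gives no r, so these values are assumptions:

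| r between visits | Family-wise error |
|---|---|
| 0.3 | 9.5% |
| 0.5 | 9.1% |
| 0.7 | 8.3% |

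With independent statistics it would be 1 − 0.95² = 9.75%.

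**4. Score against change.** With SD 2.0 at each visit and baseline/follow-up correlation ρ (also an assumption), the SD of change is 2.0 × √(2(1 − ρ)). Power is for the two-sided t-test, difference 1.0, 32 per group:

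| Outcome | SD | Power |
|---|---|---|
| Score at follow-up | 2.00 | 50% |
| Change, ρ = 0 | 2.83 | 29% |
| Change, ρ = 0.3 | 2.37 | 38% |
| Change, ρ = 0.5 | 2.00 | 50% |
| Change, ρ = 0.7 | 1.55 | 72% |

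Change loses power below ρ = 0.5, breaks even at 0.5 and gains above it. Low correlations are plausible where baseline and follow-up concern different regimens, but the article has no data on this. Baseline as a covariate avoids the question: the residual SD is 2.0 × √(1 − ρ²), which never exceeds 2.0.

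**The case against.** Several points on the other side are sound.

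- **Section 5.9 is probably not a rival primary endpoint.** The words stand under the readmission heading, and the next sentence makes the category-specific readmission rates secondary. The natural reading is a ranking within that measure. A reader might infer four competing primary endpoints; the text supports three conflicting adherence definitions and one loose phrase.
- **One test is named.** Section 2.4 gives instrument, contrast, timing, test and alpha. It would be too strong to say that the trial has no pre-specified test. What stands is that the abstract and section 3 contradict it and section 5.10 does not carry it forward.
- **The 1-month visit is an isolated slip.** An error rate computed over three visits would describe a schedule that does not exist. Even the two-visit figure is conditional, because the article never says that either visit suffices.
- **Change does not always lose power.** The table in the working shows no loss at 0.5 and a gain at 0.7.
- **The baseline is not empty for everyone.** The Introduction counts blood pressure, glucose and lipid treatment as secondary prevention and says these patients often have chronic diseases and several medicines. Many may already take such drugs. One might also infer that untreated patients start with a falsely good score and then appear to worsen. The article's own figures do not show this: item 7 is reverse scored, so answering not at all throughout gives 6 × 1 + 4 = 10, exactly the control mean assumed in section 2.4.

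An analysis plan that is not shown could add detail, but it does not excuse contradictory statements of the primary outcome in the protocol itself.

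**Conclusion.** The inconsistency is real and should be corrected. The abstract, section 2.4 and section 3 give three different primary outcomes, and section 5.10 assigns a test to none of them. This rests on the printed text alone.

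The sizes rest on assumptions. The family-wise error is about 8-10% only if success at either visit may be claimed, with between-visit correlation 0.7 to 0.3. Power for change runs from 29% to 72% over baseline/follow-up correlations of 0 to 0.7, against 50% for the score. The conclusion is that the two forms are not interchangeable, not that change is always worse.

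The baseline point is an inference and a supporting reason. Baseline ARMS-7 reflects any pre-stroke regimen and may not be meaningful for patients on no medicines, whose share is unknown. That is a further reason not to define the primary outcome as change.

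**What to change.** 1. State one primary outcome in the abstract and in sections 2.4 and 3: the between-group difference in ARMS-7 total score at 6 months. This is the last scheduled visit and so matches the end of the study period in section 2.4, which should name the month. If the investigators prefer 3 months, when the intervention ends, they should say so and use that visit throughout.
2. Name the test for this outcome in section 5.10.
3. Make the 3-month comparison secondary and delete the 1-month assessment from the abstract.
4. Reword section 5.9 so that all-cause readmission is a secondary outcome of the trial, with its categories below it.
5. Use baseline ARMS-7 only as a covariate. Add an indicator for patients on no medication before the stroke, with a constant fill-in value for their baseline score. Without a fill-in value they would drop out of the model, against the plan to analyse everyone as randomised.

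The cost is wording in the abstract and sections 2.4, 3, 5.9 and 5.10, plus one yes/no baseline item; Table 2 already collects the number of medications taken. No visit or patient is added. The one real concession is that the 3-month result no longer counts as primary.
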